### Follow-Up

Outcome information is collected at baseline, at 6, and at 12 months via telephone calls with patients or relatives conducted by a blinded study team member, and through FIRE database exports. The study team will make every reasonable effort to keep each patient in the study until all planned treatments and assessments have been performed. But patients may withdraw from the study or be withdrawn when they are lost to follow-up.

### Assessment of primary outcome

The primary endpoint is medication appropriateness, measured jointly by the MAI and the AOU, in each study group. While the AOU assesses underprescribing, the MAI is a tool to assess different elements of medication prescribing (eg, overprescribing, drug–drug interactions, etc).^7 39 40^

Blinded study team members assess the MAI for each regular medication study participants take and assess the AOU for each chronic condition study participants have. The investigators will use the weighted 10-item version of the MAI developed by Samsa *et al.*
40 However, due to the rapidly changing drug prices the MAI item on cost-effectiveness will not be included. The criteria of the MAI, including corresponding weights, can be found in table 2. Using clinical data and the predefined operational definitions for each item, the assessor rates each medication on a three-point scale ranging from A=appropriate, B=marginally appropriate, C=inappropriate. Each ‘inappropriate’ rating will receive the respective weight from table 2, while the weight of ratings ‘appropriate’ and ‘marginally appropriate’ will be 0. Thus, the score for each medication ranges from 0 to 17 (as the cost-effectiveness criterion will not be included).^40^ A higher score indicates a greater degree of medication inappropriateness. The investigators will calculate the score for each medication and then calculate the summated score for each patient, by summing up the scores for each medication. For the AOU, assessors decide for each chronic condition if there is (i) no omission, (ii) marginal omission, or (iii) omission of indicated medication.^41–43^ For each patient, the investigators will calculate how many omissions there are.

**Table 2 T2:** Criteria of the Medication Appropriateness Index including weights

	Item	Weight
1	Is there an indication for the drug?	3
2	Is the medication effective for the condition?	3
3	Is the dosage correct?	2
4	Are the directions correct?	2
5	Are the directions practical?	1
6	Are there clinically significant drug–drug interactions?	2
7	Are there clinically significant drug–disease/condition interactions?	2
8	Is there unnecessary duplication with other drug(s)?	1
9	Is the duration of therapy acceptable?	1

Item 10 ‘Is this drug the least expensive alternative compared to others of equal utility?’ has been excluded.^40^

The MAI and the AOU will be assessed and calculated for baseline, the follow-up one at 6 months and the follow-up two at 12 months. For at least 32 cases (10% of the targeted sample size), two blinded investigators will conduct a blinded independent double assessment of the MAI and the AOU to check inter-rater reliability. The investigators will use information about diagnoses (coded in ICPC-2) and medication intake from the FIRE database for these assessments.

### Assessment of secondary outcomes

The following secondary outcomes are assessed at baseline, 6 and 12 months (data source in brackets)

Degree of polypharmacy; that is, the number of regular long-term medications patients take (FIRE database).Degree of overprescribing, measured by the MAI (assessment of FIRE data done by study team).Degree of underprescribing, measured by the AOU (assessment of FIRE data done by study team).Number of falls and fractures in the last six months (patient/relative phone call).Quality of life, based on the five-level version of the European Quality of Life-5 Dimensions questionnaire, including pain/discomfort^44 45^ (patient/relative phone call).Amount of formal care received in the last six months: number and length of stay of planned and unplanned hospitalisations; visits to the emergency room without inpatient hospitalisation; GP visits; medical specialist visits (differentiated by specialty); hospital outpatient visits; inpatient stays; length of stay at rehabilitation facilities; physiotherapist and other allied therapist visits; nursing home admissions (in patients who were living in the community at baseline); length of stay in nursing homes; and, number of home nursing visits (patient/relative phone call, except for number of GP visits which comes from FIRE database).Amount of informal care received in the last six months: unpaid care by, for example, family members, relatives, friends (patient/relative phone call).Survival (patient/relative phone call or reported by GP).QALYs accrued in one year,^46^ measured as a function of the length and the quality of life (calculated based on data from patient/relative phone call).Direct medical costs accrued in one year, measured by combining formal and informal healthcare resource use observed in the trial (patient/relative phone call), including the time GPs spend on the intervention (reported by GP) and software costs (literature search), and Swiss unit costs from sources external to the trial (literature search).Cost-effectiveness of the intervention, calculated by combining clinical data (FIRE database), quality of life data (patient/relative phone call) and healthcare use data collected in the trial (patient/relative phone call).

The following outcome will be assessed after the intervention

Percentage of STRIPA recommendations accepted and rejected by GPs (reported by GPs, cross-verified with STRIPA reports).

The following secondary outcome is assessed at baseline only:

Patients’ willingness to have medications deprescribed, measured with the validated ‘revised Patient Attitudes Towards Deprescribing’questionnaire^47 48^ (patient/relative phone call).

Safety outcomes include adverse events, serious adverse events and device deficiencies.

### Study duration

GPs can recruit the patients over a period of at least six months, so they can integrate recruitment into their daily practice. Recruited patients are followed up for one year.

### Sample size

Sample size calculation is based on testing the two co-primary outcomes for superiority and uses the Bonferroni-approach to account for multiple testing. Based on trial results published by Gallagher *et al* in 2011, the investigators assumed that 35% of patients in the control group and 60% of patients in the intervention group will improve their total MAI score (at least one less point) and that 10% of patients in the control group and 30% of patients in the intervention group will have a better AOU score (at least one fewer prescribing omission).^49^ Intracluster correlations (ICC) of 0.01–0.05 are typically found for binary outcomes in elderly individuals.^50^ The investigators conservatively assumed an ICC of 0.05 to calculate the sample size. The investigators fixed the type I error at a Bonferroni-corrected two-sided alpha level of 0.025.

Based on a two-sample comparison of proportions and a prespecified number of clusters of about 40 (about 20 per arm), seven patients per cluster are required to detect a difference of 25% between the two groups in the proportion of improvement in the MAI, with a power of 90%. The number of 40 GPs was selected arbitrarily for feasibility reasons. Using the same assumption for the AOU, the investigators found they also need seven patients per cluster to detect a difference of 20%. The investigators thus need a sample of 280 patients (140 per arm) to provide 81% power to detect a significant improvement in both the MAI score and the AOU. To account for attrition from dropout or death (15% estimated), the number of patients per cluster was increased to eight (max. ten), so the final sample size should be about 320 patients (160 per arm). The investigators will closely support GPs to help them reach the target sample size.

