### Statistical analysis

In case data on outcomes are incomplete, the investigators will use multiple imputation to replace missing values, taking data clustering into account. No interim analyses are planned.

There are two co-primary outcomes: improvement in the MAI at 12 months, defined as decrease of at least one point, and improvement in the AOU at 12 months, defined as at least one less prescribing omission. Both outcomes will be tested separately; success is indicated by the significance of at least one of the two tests.

For the co-primary outcomes, the investigators will present and compare the proportion of patients whose MAI and AOU score improved in the control and intervention group. The relative difference between groups will be determined in a mixed-effects logistic model with a random intercept at the GP level to account for clustering. The effect measure for the primary outcomes will be odds ratios (OR). The relative difference will be presented as OR with a 95% CI. The primary analysis will be an intention-to-treat analysis. In a per-protocol analysis, the investigators will only evaluate patients who adhered to the protocol and exclude patients who violate any inclusion or exclusion criteria.

Secondary binary outcomes will be evaluated like the primary outcomes. Secondary continuous outcomes will be analysed using random-effects linear regression with a random intercept at the GP level. Models will also be adjusted for the baseline value as a covariate. Secondary count outcomes will be analysed using random-effects Poisson regression with a random intercept at the GP level.

Health economic analyses will assess (i) resource use and cost differences between the trial arms, (ii) differences in quality-adjusted lifetime between the trial arms, expressed as QALYs, and (iii) a comparison of cost-effectiveness between intervention and standard care.

Because cluster-randomisation may not balance characteristics between groups to match individual-level randomisation, the investigators will adjust each model for patient-level and physician-level variables to account for case-mix differences between groups and potential recruitment bias in a sensitivity analysis. They will also account for the correlated nature of data among GPs by using multilevel mixed-effects models. Unadjusted models will be provided for information only.

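### The only overall power quoted (81%) is for both outcomes being significant, while success needs only one; no power is given for the rule that decides success

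*Protocol article*

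**What the plan says.** The Sample size section of the protocol article treats MAI and AOU as two co-primary outcomes and "uses the Bonferroni-approach to account for multiple testing", which gives a "Bonferroni-corrected two-sided alpha level of 0.025" for each test. It assumes that "35% of patients in the control group and 60% of patients in the intervention group will improve their total MAI score" and that "10% of patients in the control group and 30% of patients in the intervention group will have a better AOU score". The authors "conservatively assumed an ICC of 0.05 to calculate the sample size", fix about 40 clusters (about 20 per arm), and find that each outcome needs seven patients per cluster for 90% power. That gives 280 patients, 140 per arm. The section then ties this number to an overall power: the sample is needed "to provide 81% power to detect a significant improvement in both the MAI score and the AOU".

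The Statistical analysis section states the decision rule. The two outcomes are tested separately and "success is indicated by the significance of at least one of the two tests".

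The Assessment of primary outcome section words the endpoint as a single construct: "The primary endpoint is medication appropriateness, measured jointly by the MAI and the AOU".

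**The concern.** Two different rules can apply to a pair of primary outcomes. If one significant test is enough, alpha must be split or otherwise protected, and the relevant power is the probability that at least one test is significant. If both must be significant, no alpha split is needed, and the relevant power is the probability that both are. Here the alpha and the success rule follow the first logic, and the overall power figure follows the second. The sentence that justifies 280 patients therefore describes an event that the trial does not require, and the power of the event that it does require is not stated.

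What is at stake is interpretation. Suppose that only MAI is significant. The Statistical analysis section calls that a success. A reader who starts from the 81% for both outcomes, and from an endpoint described as jointly measured, may conclude that appropriateness improved on both sides, including underprescribing. It is better to settle the wording before results are known.

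**Working it through.** **Inputs**, all from the Sample size section: MAI improvement 35% v 60%; AOU improvement 10% v 30%; ICC 0.05; 20 clusters per arm; two-sided alpha 0.025 per test (z = 2.241); 90% power per outcome. The section names no formula, so the standard pooled two-proportion formula is used below, with and without continuity correction.

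**1. Reproducing seven per cluster and 280.** Let n be the number per arm needed under individual randomisation. The cluster size m must satisfy 20m / (1 + (m − 1) × 0.05) ≥ n, so m ≥ 0.95n / (20 − 0.05n).

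| Outcome | Continuity correction | n per arm | m |
|---|---|---|---|
| MAI | no | 97 | 6.08 |
| AOU | no | 98 | 6.17 |
| MAI | yes | 105 | 6.76 |
| AOU | yes | 107 | 6.94 |

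Every row rounds up to 7, and 40 × 7 = 280. The plan's sample size reproduces from 90% power per outcome alone; the 81% is not an input.

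**2. Reproducing the 81%.** 0.90 × 0.90 = 0.81. This is the probability that both tests are significant if each has exactly 90% power and the two are independent.

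**3. Power reached with seven per cluster.** The design effect is 1 + 6 × 0.05 = 1.30, so the effective number per arm is 140 / 1.30 = 107.7. P1 is the power for MAI and P2 the power for AOU. The last two columns assume independence.

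| Method | P1 | P2 | Both, P1 × P2 | At least one, 1 − (1 − P1)(1 − P2) |
|---|---|---|---|---|
| Nominal | 90% | 90% | 81% | 99% |
| With correction | 91.0% | 90.3% | 82.1% | 99.1% |
| Without correction | 93.0% | 93.0% | 86.5% | 99.5% |

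**4. Dependence between the tests.** The documents give no correlation between the MAI and AOU test statistics, so the values here are assumptions. In general, P(at least one) = P1 + P2 − P(both), and it cannot be smaller than the larger of P1 and P2. With nominal 90% per outcome and bivariate normal test statistics:

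| Assumed correlation | Both | At least one |
|---|---|---|
| 0 | 81.0% | 99.0% |
| 0.3 | 82.2% | 97.8% |
| 0.5 | 83.2% | 96.8% |
| 0.8 | 85.6% | 94.4% |
| Floor under any dependence | – | 90% |

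With the power actually reached at seven per cluster, the floor for at least one is 91% (with correction) or 93% (without).

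**5. Type I error.** Two tests at 0.025 give a familywise error of at most 0.05 (0.0494 if independent). This is correct for the at-least-one rule.

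**6. Holm for comparison** (smaller p-value at 0.025, then the other at 0.05). The first rejection still needs p ≤ 0.025, so the power for at least one does not change. Write P1′ and P2′ for the powers at alpha 0.05. Under independence, power for both = P1′P2′ − (P1′ − P1)(P2′ − P2).

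- Without correction: 0.9616 × 0.9612 − 0.0312 × 0.0314 = 0.923, against 0.865 with Bonferroni.
- With correction: 0.9483 × 0.9440 − 0.0387 × 0.0410 = 0.894, against 0.821 with Bonferroni.

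**The case against.** The best defence is that nothing operational is wrong. Each outcome is sized separately at 90% power and alpha 0.025, both need seven per cluster, and 280 follows. The decision rule is stated once and clearly, Bonferroni is valid for it, and the 81% sentence names the event that it refers to. On this view the 81% is supplementary information, and the joint wording of the endpoint only says that two instruments cover one construct.

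Most of this stands. It settles that alpha, test structure and success rule agree with each other. It does not remove the mismatch, because the 81% is not offered as an aside: the sentence presents it as what the 280 patients are needed for, and no figure is given for the rule that decides success.

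Two stronger readings are tempting, and the document supports neither. A reader might infer that 81% is an arithmetic error, because seven per cluster gives 93% per outcome and 86.5% for both. Those figures hold only without continuity correction, and the section names no formula. With correction the product is 82.1%, and 81% is exactly the product of the two nominal targets. A reader might also infer that the Bonferroni split is a mistake. It is not: it controls the familywise error for the stated rule, and Holm is only a more efficient alternative.

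**Conclusion.** The point holds as a mismatch between the power statement and the success rule. The quoted 81% is correct as a nominal figure for both outcomes under independence, an assumption that the section leaves unstated. The rule in force has at least 90% power whatever the dependence, and about 99% if the tests are independent. These figures rest on the plan's own improvement rates, ICC and cluster numbers.

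The direction is conservative. It would be wrong to conclude that the trial is underpowered, that its type I error is inflated, or that 280 needs to change. The consequence is confined to how the design is described and how a result on one outcome alone would be read. Severity: minor to moderate.

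**What to change.** 1. In Sample size, state the power for at least one significant test at 0.025: at least 90% whatever the dependence, about 99% if the tests are independent. Say that the MAI–AOU correlation is not known.
2. Keep the 81%, but label it as the nominal power for both outcomes under independence. If the power reached at seven per cluster is preferred, give 82% with or 87% without continuity correction, and name the formula.
3. In Assessment of primary outcome, and where the Abstract uses the same joint wording, describe MAI and AOU as two primary outcomes tested separately. Add that the conclusion is limited to the outcome that is significant.
4. Optional, as an improvement and not a correction: replace Bonferroni by Holm. The familywise error stays at 5%, the power for at least one is unchanged, and the power for both rises from 82–87% to about 89–92% under independence. The small price is that matching simultaneous confidence intervals are less simple.

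Items 1 to 3 are wording only. Item 4 changes the testing rule and should be fixed before results are known. None needs extra patients.

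### Eight patients per cluster (320 in all) covers 12.5% attrition, not the stated 15%: 272 would remain, against the 280 said to be needed

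*Protocol article*

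**What the plan says.** All the figures are in the Sample size section of the protocol article.

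- Error rate: "The investigators fixed the type I error at a Bonferroni-corrected two-sided alpha level of 0.025".
- MAI assumption: "35% of patients in the control group and 60% of patients in the intervention group will improve their total MAI score".
- AOU assumption: "10% of patients in the control group and 30% of patients in the intervention group will have a better AOU score".
- Clustering: "The investigators conservatively assumed an ICC of 0.05 to calculate the sample size".
- Cluster size: "a prespecified number of clusters of about 40 (about 20 per arm), seven patients per cluster are required" for the MAI at 90% power, and the same number for the AOU.
- Total: "The investigators thus need a sample of 280 patients (140 per arm"), with 81% power to show a benefit on both outcomes.
- Attrition: "To account for attrition from dropout or death (15% estimated), the number of patients per cluster was increased to eight (max. ten").
- Target: "so the final sample size should be about 320 patients (160 per arm").

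The Screening and enrolment section and Table 1 repeat the range of eight to ten patients per GP. The section on assessing the primary outcome sets at least 32 double assessments and calls this 10% of the target sample, so 320 is used there too.

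**The concern.** The article treats 280 as the number needed once losses have occurred, because it adds an allowance for loss on top of it. The allowance should then return 280 when the stated loss is applied, and it does not. The target of 320, the attrition of 15% and the requirement of 280 cannot all hold.

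What is at stake is the coherence of the sample size statement. A trial that enrolled exactly its target and lost exactly the predicted share would fall short of its own stated requirement, and readers of the results will compare achieved numbers with these figures.

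**Working it through.** **Inputs** (Sample size section): two-sided alpha 0.025 per outcome; MAI 35% v 60%; AOU 10% v 30%; ICC 0.05; 20 clusters per arm; power 90% per outcome; attrition 15%; eight per cluster after inflation.

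**1. Reproduce the figure before attrition.** For two proportions with pooled variance under the null, the number per arm without clustering is

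n = [z(0.9875)·√(2p̄(1−p̄)) + z(0.90)·√(p₁(1−p₁)+p₂(1−p₂))]² / (p₁−p₂)².

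Setting 20m = n·[1 + (m−1)·0.05] and solving gives m = 0.95n / (20 − 0.05n).

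| Outcome | Continuity correction | n per arm | m | Rounded up |
|---|---|---|---|---|
| MAI | no | 97 | 6.08 | 7 |
| MAI | yes | 105 | 6.76 | 7 |
| AOU | no | 98 | 6.17 | 7 |
| AOU | yes | 107 | 6.94 | 7 |

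Every variant gives seven per cluster, so 7 × 40 = 280. The joint power is 0.90 × 0.90 = 0.81. The article's figures before attrition are reproduced.

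**2. Check the allowance for loss.**

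- Remaining from the target: 320 × 0.85 = 272, and 8 × 0.85 = 6.8 per cluster.
- Shortfall: 280 − 272 = 8 patients; 8/280 = 2.9%.
- Loss that 320 can bear: 1 − 280/320 = 12.5%.
- Enrolment that leaves 280 after 15% loss: 280/0.85 = 329.4, so 330. Per cluster: 7/0.85 = 8.24.

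**3. Power at 272.** With m = 6.8 the design effect is 1 + 5.8 × 0.05 = 1.29, and the effective number per arm is 136/1.29 = 105.4. With m = 7 it is 140/1.30 = 107.7. For the continuity-corrected version, the effective number N is replaced by N − 2/d + 1/(N·d²), where d is the difference in proportions. Joint power is the product of the two, as in the article.

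| Evaluable | Formula | MAI | AOU | Joint |
|---|---|---|---|---|
| 280 | uncorrected | 93.1% | 93.0% | 86.5% |
| 272 | uncorrected | 92.5% | 92.4% | 85.5% |
| 280 | corrected | 91.0% | 90.3% | 82.1% |
| 272 | corrected | 90.3% | 89.6% | 80.8% |

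If random loss makes clusters unequal (binomial thinning of eight), joint power at 272 becomes 85.2% uncorrected and 80.5% corrected.

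**The case against.** The strongest reply is that the text is approximate and leaves room. It speaks of about 40 clusters, about 320 patients and an estimated loss, and it lets each GP recruit up to ten. An average of 8.24 per cluster meets the requirement and lies inside that range; at nine per cluster, 360 enrolled leaves 306. This shows that the correction needs no change of design. It does not make the printed target right, because 320 is eight times 40, and eight is the number offered as the answer to 15% loss. Nor does the planned multiple imputation settle it: the sample size section itself counts 280 after loss.

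A second reply is that almost nothing is lost in power, and that the Statistical analysis section counts success on either outcome as enough. Both stand, and they limit the weight of the point.

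Four stronger readings are tempting, and the document does not support them:

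- **The trial is underpowered.** It is not shown to be. Rounding up to seven absorbs the shortfall in full without continuity correction. With it, AOU and joint power fall below their stated values by only 0.4 and 0.2 percentage points.
- **Enrolment would stop at 320.** No rule says so. Recruitment runs by cluster, and a cluster may hold up to ten. The status section puts 278 patients at about 85% of target, which implies about 327 (278/0.85); 278/320 would be 86.9%.
- **The reported pace makes a higher target automatic.** Dividing 278 patients by 31 randomised GPs gives about 9 each, and about 359 from 40 GPs. This assumes that all 278 belong to those 31 GPs. GPs are randomised only once their cluster is complete, so others may hold some of them: 31 clusters of eight account for 248, leaving 30 elsewhere.
- **The figure comes from multiplying by 1.15.** That gives 322, close to 320, but rounding 8.24 to the nearest whole patient gives eight as well. The cause cannot be known from the text.

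**Conclusion.** The point holds as a minor error of arithmetic in a stated figure. At eight patients in each of 40 clusters and 15% attrition, 272 evaluable patients remain where the section asks for 280, and 320 covers 12.5% attrition. This comparison of enrolled, lost and remaining patients needs nothing beyond the article's own numbers.

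The effect on power is very small: about half a percentage point per outcome without continuity correction, and 0.7 with it. The article does not say which formula it used, so whether 272 keeps every stated power level depends on that choice. The power figures assume an ICC of 0.05, two-sided alpha 0.025, 20 equal clusters per arm, and joint power as a simple product. No conclusion about the validity of the design follows.

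**What to change.** Either of two changes makes the section consistent.

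1. **Restate the target as about 330**, an average of about 8.24 per cluster. For example, 30 GPs with eight patients and ten GPs with nine give 240 + 90 = 330. The range of eight to ten per GP stays as it is. The number of double assessments tied to 10% of the target would become 33, and any other place that repeats 320 should follow.
2. **Keep 320 and say that it allows for 12.5% attrition.** Add that 15% loss would leave 272, and give the power there with the formula named: about 92.5% (MAI), 92.4% (AOU) and 85.5% (joint) without continuity correction, or about 90.3%, 89.6% and 80.8% with it.

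The second costs a sentence. The first costs a corrected figure and about 10 more patients than the present target, within the cluster cap already allowed.
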